### Interim analysis

Initially, two interim analyses (i.e., after 200 and 700 patients) were scheduled; however, one interim analysis at 300 patients was therefore decided to assess for protocol compliance, main outcome, and SAEs, according to data collection completeness. An independent statistician, who has access to the whole database, reported these data to the DMSC by maintaining the blinding for the study groups (i.e., group A vs. group B). After the analysis of this report, the DMSC sent a report to continue the study recruitment without any safety issue.

### Statistical methods: plans to give access to the full protocol, participant-level data, and statistical code

No later than 3 years after the collection of the primary outcome of the last included patient, a completely deidentified dataset will be shared into an appropriate data archive for any scientific and reproducibility purposes.

## Methods: oversight and monitoring

### Composition of the coordinating center and trial steering committee

The principal investigator will have the responsibility for the study management. The study executive committee consists of the principal investigator, project coordinator, and research nurse, who are all affiliated to the Hôpital Erasme in Brussels (Belgium). The executive committee will be responsible for the daily running of the trial. The trial steering committee consists of the member of the Neuro-Intensive Care Section of ESICM, who meet twice a year (except during the pandemic) to have an update of the study.

### Composition of the data safety monitoring committee, its role, and reporting structure

The study is considered as a low-risk study; a Data Monitoring Safety Committee (DMC) has been created to perform the interim analyses for safety, futility, or efficacy so that the executive and steering committee can remain blinded for the study outcomes. All the DMSC members (Supplemental Table 2) have no conflict of interest with the sponsor of the study and are not involved in the study. DMSC membership is for the duration of the clinical trial. The DMSC has therefore monitored inclusion rate, losses to follow-up, or potential harms, making the recommendation that the trial continues to recruit participants or whether recruitment should be terminated earlier.

**Table 2 Tab2:** Serious adverse event (SAE) of the TRAIN study

SAE	Definition
Severe hypertension	Mean arterial pressure (MAP) > 130 mmHg for more than 1 h and needing active therapy, in the absence of vasopressor agents and increased intracranial hypertension
Severe hypotension	MAP < 65 mmHg for at least > 1 h, not responding to fluid therapy and needing vasopressor therapy, in the absence of active bleeding
Venous thrombotic events	Deep vein thrombosis (formation of a blood clot within a deep vein in the legs or arms, which may be associated with non-specific signs, such as pain, swelling, redness, warmness, and engorged superficial veins—it can be diagnosed either by echography, venography, or CT imaging); pulmonary embolism (formation of a clot within the pulmonary arterial circulation, diagnosed by contrast pulmonary CT scan or echocardiography)
Acute myocardial ischemia	Acute myocardial infarction (ST-elevation and non-ST-elevation myocardial infarction) or unstable chest pain diagnosed during current hospital admission, according to specific criteria (i.e., elevated biomarkers of myocardial injury, ischemic signs on ECG, clinical suspicion) and the patient has received specific treatment (reperfusion strategies such as percutaneous coronary intervention [PCI] or thrombolysis) or initiation/increase of antithrombotic drug treatment during current ICU admission
Intestinal ischemia	Ischemic lesions confirmed by endoscopy and/or open surgery
Acute peripheral limb ischemia	Clinical signs and the need for open or percutaneous vascular intervention, amputation, or initiation/increased antithrombotic treatment
Anaphylactic reaction to RBC transfusion	Muco-cutaneous signs (i.e., urticaria, pruritus) and/or hemolytic anemia within 24 h after transfusion
ARDS	Acute hypoxemia with bilateral infiltrates, according to recent definitions
TRALI	ARDS occurring within 6 h after RBC transfusion
TACO	Acute hypoxemia (PaO_2_/FiO_2_ < 300 regardless of positive end-expiratory pressure [PEEP]) with bilateral lung infiltrates and occurrence within 6 h after RBC transfusion and increased blood pressure and positive fluid balance
Sepsis	Presence of an infection and organ failure attributed to it. Septic shock = arterial hypotension (MAP < 65 mmHg) despite adequate fluid resuscitation and necessitating vasopressor therapy
Infections	According to CDC definitions
Brain tissue hypoxia	For those patients with P_bt_O_2_ monitoring, values of < 20 mmHg for at least 1 h over the last 24 h

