### Interventions: description

Patients are randomized to two different thresholds of Hb to determine when RBC transfusion should be initiated (< 7 g/dL vs. < 9 g/dL). After randomization, all patients should preferably receive one unit of RBC at a time. Patients randomized to the lower Hb threshold for transfusion receive packed RBC transfusion whenever their Hb concentration is < 7 g/dL; similarly, patients randomized to the higher threshold are transfused whenever their Hb concentration is < 9 g/dL. Transfusion thresholds are maintained until a maximum of 28 days after randomization or hospital discharge/death, whichever occurs first. Daily Hb concentrations are recorded according to local practices; values from blood gas analyses are also allowed during the ICU stay to avoid protocol violation. Patients can be included in the study only once.

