#### Interventions: modifications

Protocol violation is defined as one of the following: (a) inability to maintain the daily max Hb values < 9 g/dL in the restrictive group and avoid transfusion until Hb drops below 7 g/dL OR > 9 g/dL in the liberal group for two consecutive days, (b) one or more transfusions given inappropriately (i.e., in contradiction of the assigned trigger level), and (c) error in type/cross-match between donor and recipient.

Crossover to another treatment arm than allocated is allowed based on the decision of the treating physician, such as (1) acute coronary syndrome, requiring a higher Hb level; (2) acute bleeding requiring multiple RBCT; and (3) lack of available blood. The reason for crossover or protocol violation will be mentioned in the electronic case report form (eCRF).

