## Methods: participants, interventions, and outcomes

### Study setting

This study will be conducted in 72 intensive care units (ICUs) worldwide. The complete list of recruiting sites is shown in Supplemental Table 1. The selection of participating ICUs was initiated within the Neuro-Intensive Care (NIC) Section of the European Society of Intensive Care Medicine (ESICM), with the identification of national investigators who then selected potential academic and non-academic ICUs with neurosurgical facilities and an adequate number of patients (> 50) with acute brain injury admitted per year. The study was initially expected to last 4 years, assuming the inclusion of 75–95 patients/month in 50–70 different centers. The final duration of the study will be almost 7 years, because of the slow recruitment rate, which is in part due to the recent pandemic crisis.

**Table 1 Tab1:** Inclusion and exclusion criteria of the TRAIN study

Inclusion criteria	Exclusion criteria
TBI, SAH, or ICH	Other neurological diseases, such as ischemic stroke or post-anoxic coma; status epilepticus without underlying brain injury; CNS infections (community-acquired; hospital-acquired; ventriculitis; post-operative)
Age ≥ 18 and ≤ 80 years	
GCS ≤ 13 on randomization	Known previous neurological disease, causing significant cognitive and/or motor handicap
Expected ICU stay > 72 h	ICH due to AVM or brain tumor
Hb ≤ 9 g/dL within 10 days from brain injury	Inability (religious reasons) or reduced ability (lack of compatible blood) to receive blood products
	Active and uncontrolled bleeding at the time of enrollment
	GCS of 3 with both pupils fixed and dilated; brain death or imminent death (within 24 h)
	Pregnancy
	Medical need to correct anemia (e.g., active coronary disease or severe cardiac disease) with target Hb levels > 9 g/dL
	DNE orders
	Previous allo-immunization due to transfusion, limiting RBC availability

*GCS*, Glasgow Coma Score; *ICU*, intensive care unit; *Hb*, hemoglobin; *DNE*, do-not-escalate (i.e., vasopressors, mechanical ventilation, renal replacement therapy); *CNS*, central nervous system; *ICH*, intracranial hemorrhage; *AVM*, arterio-venous malformation; *TBI*, traumatic brain injury; *SAH*, subarachnoid hemorrhage

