### Eligibility criteria

All patients admitted to the ICU with TBI, SAH, or intracerebral hemorrhage (ICH, either primary or anticoagulant-associated) are screened for study eligibility within the first 10 days after the initial injury. Patients are eligible regardless of their need for surgical intervention or RBCT for acute bleeding. Anemia is defined as Hb ≤ 9 g/dL and should occur within this time period. If a patient is considered as not eligible, the reason is recorded as for eligible patients who decide not to participate. No other specific information is recorded for such patients. Inclusion and exclusion criteria are shown in Table 1 and are checked by the attending physician and confirmed by the local investigator.

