### Informed consent

Written informed consent must be obtained prior to the randomization to the study. Because of the difficulties predicting the exact moment at which anemia may occur during the ICU stay, it is recommended that written informed consent be obtained as soon as possible after ICU admission so that randomization can be performed rapidly when the inclusion criteria are met. For patients who are unable to consent, their legal representatives are informed of the study as soon as possible and must sign for participation in the trial before randomization. Subjects with sufficient neurological recovery are informed of their study participation and be asked to provide their consent for the use of their data. Patients or next of kin can withdraw consent at any time during the study without giving a specific reason. Withdrawal should not influence the standard of care, with an Hb threshold for RBC transfusion that will then be decided by the attending physician. Patients withdrawing from the study are asked to consent for the inclusion of data collected before withdrawal. The site investigator may also withdraw a subject from the study for safety reasons (e.g., acute myocardial infarction needing higher Hb levels).

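### The myocardial-ischemia SAE depends on the treatment given, so an infarction answered only by a higher hemoglobin is left out of the safety count

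*Protocol article*

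**What the plan says.** The event is defined in Table 2 of the protocol article, under the section on the data safety monitoring committee. The patient must have an infarction or "unstable chest pain diagnosed during current hospital admission", supported by biomarkers, ECG signs and clinical suspicion. In addition, the definition requires that the "patient has received specific treatment (reperfusion strategies such as percutaneous coronary intervention [PCI] or thrombolysis) or initiation/increase of antithrombotic drug treatment" took place in the current ICU admission. The section on adverse event reporting calls Table 2 the complete SAE list and says that death is not reported as an SAE.

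Two other sections say what may follow a coronary event. Under Interventions: modifications, crossover to the other arm is allowed for "1) acute coronary syndrome, requiring a higher Hb level", and "The reason for crossover or protocol violation will be mentioned in the electronic case report form (eCRF"). Under Informed consent, "The site investigator may also withdraw a subject from the study for safety reasons (e.g., acute myocardial infarction needing higher Hb levels"). No section says that a crossover or withdrawal for a coronary reason is also entered as an SAE.

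**The concern.** Whether an infarction counts depends on how it was managed as well as on whether it happened. The two responses that the protocol itself names, crossover and withdrawal for a higher Hb, are not on the list of qualifying treatments. A site can therefore follow the protocol, diagnose an infarction, record a crossover or withdrawal, and have no SAE to enter. A fatal infarction that received neither reperfusion nor antithrombotic treatment is also absent from the SAE count.

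Myocardial ischemia is a plausible harm of tolerating a lower Hb, so it belongs in the comparison of harms between these two strategies. The trial is open-label. The staff whose choices decide whether an event counts know the allocation, and if those choices differ by arm, the comparison of harms differs with them. SAE counts have already been used: they were part of the interim analysis, and its finding of no difference in harms is the stated reason for tying later SAE reports to the safety committee to the ethics committee's annual evaluation.

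**Working it through.** The protocol states no rate or count of myocardial ischemia, so there is no figure to reproduce. The check has two parts: the text, then an illustration with assumed rates.

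**1. Which responses meet the Table 2 clause**

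| Response to a diagnosed event | Where named | Counted as SAE? |
|---|---|---|
| Reperfusion in the ICU | Table 2 | Yes |
| Antithrombotic drug started or increased in the ICU | Table 2 | Yes |
| Crossover for a higher Hb, nothing else | Interventions: modifications | No |
| Withdrawal for a higher Hb, nothing else | Informed consent | No |
| Crossover or withdrawal plus a Table 2 treatment | Combination | Yes |

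**2. Which arm can lose events**

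- The treatment clause is the same in both arms, so an infarction without qualifying treatment is missed in either.
- Crossover: the triggers are below 7 g/dL (restrictive) and below 9 g/dL (liberal; "patients randomized to the higher threshold are transfused whenever their Hb concentration is < 9 g/dL"). Reaching a higher Hb by switching arm is possible only from restrictive to liberal.
- Withdrawal is not limited to one arm. An exclusion criterion in Table 1, "Medical need to correct anemia (e.g., active coronary disease or severe cardiac disease) with target Hb levels > 9 g/dL", shows that the protocol foresees cardiac targets above the liberal trigger.

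One of the two uncounted routes is therefore one-sided and the other is not.

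**3. What unequal loss would do**

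Let p_R and p_L be the true event rates in the restrictive and liberal arms, and m_R and m_L the shares missed. Then

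observed risk ratio = (p_R / p_L) × (1 − m_R) / (1 − m_L).

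The planned 397 per arm (Sample size) serves only to turn rates into counts. All rates and missed shares below are assumptions.

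| True rates R / L | True ratio | Missed R / L | Expected counts R / L | Observed ratio |
|---|---|---|---|---|
| 5% / 5% | 1.00 | 30% / 0% | 13.9 / 19.9 | 0.70 |
| 5% / 5% | 1.00 | 50% / 0% | 9.9 / 19.9 | 0.50 |
| 5% / 2% | 2.50 | 30% / 0% | 13.9 / 7.9 | 1.75 |
| 5% / 2% | 2.50 | 50% / 0% | 9.9 / 7.9 | 1.25 |
| 5% / 2% | 2.50 | 70% / 0% | 6.0 / 7.9 | 0.75 |
| 5% / 2% | 2.50 | 50% / 30% | 9.9 / 5.6 | 1.79 |
| 5% / 2% | 2.50 | 30% / 30% | 13.9 / 5.6 | 2.50 |

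Example: 2.50 × (1 − 0.50) / (1 − 0.30) = 2.50 × 0.714 = 1.79.

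Only a difference between m_R and m_L moves the ratio. With equal shares the ratio holds, but the absolute difference shrinks: at 30% missed in both arms it falls from 3.0 to 2.1 percentage points (3.0 × 0.70). The rows with no liberal-arm loss are extreme cases, because the clause also excludes untreated events in that arm.

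**The case against.** The strongest reply is that no bias between arms has been shown. A reader might infer that the missed events fall in the restrictive arm and that the trial is therefore tilted toward finding restriction safe. The document does not support that. The clause applies equally to both arms, and withdrawal is open to both. A higher Hb does not preclude antithrombotic treatment: the protocol sets no other limits on concomitant care, and a patient who receives both is counted. Selective loss would require restrictive-arm patients to be managed by Hb alone more often than liberal-arm patients, and nothing in the text says so. The idea that antithrombotics are often withheld after brain hemorrhage is clinical reasoning that the protocol does not state, and it would apply to both arms. This part of the reply stands. What remains is that upward crossover is open to one arm only, which makes a larger loss there possible.

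A reader might also infer that pre-randomization infarctions are counted, because the definition refers to the hospital admission and patients are screened over the first 10 days after injury. This is weak. SAEs belong to the daily ICU data, the eCRF is generated for randomized patients, and any earlier events would be balanced between arms in expectation.

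Requiring treatment can also be defended as a choice for specificity, and Table 2 attaches treatment conditions to severe hypertension and hypotension too. Dropping the condition leaves criteria that include clinical suspicion, judged by unblinded staff. Counting every coronary crossover automatically would add a route open mainly to the restrictive arm and could bias the comparison the other way. These points stand and shape the fix. They do not remove the gap: diagnosed infarctions can go uncounted when the protocol is followed.

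**Conclusion.** The point holds in limited form, as a cheap improvement. As written, Table 2 leaves out a diagnosed infarction that is answered only by a higher Hb, although the protocol names crossover and withdrawal as responses to exactly that event. Such omissions can occur in either arm. They may be more frequent in the restrictive arm because only that arm can cross over to a higher Hb, but neither the direction nor the size of any net bias can be established from the document. The illustrated ratios rest wholly on assumed rates and missed shares, and equal loss in both arms would leave the ratio unchanged. Myocardial ischemia is neither the primary outcome nor a listed secondary outcome, and the eGOS analysis and the sample size are unaffected.

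**What to change.** 1. Report, by allocated arm, acute myocardial ischemia with onset after randomization that meets Table 2's diagnostic criteria regardless of treatment, beside the existing treated-only count. Readers can then see how far the comparison depends on the treatment condition.
2. Before analysis, check every crossover, withdrawal and premature-termination reason that names acute coronary syndrome or infarction against the recorded SAEs, in both arms. Add those that meet the same diagnostic criteria. Do not count a crossover as an event merely because of its stated reason.
3. State as a limitation that untreated events with no crossover or withdrawal may not be recoverable.

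The data for step 2 largely exist: the eCRF holds the crossover reason, and the reason and time of premature termination are recorded (Plans for assessment and collection of outcomes). With 791 of the planned 794 patients recruited, this is a task for data cleaning and reporting and needs no change to conduct. The cost is a small reconciliation exercise and somewhat lower specificity in the broader count, which the retained treated-only count offsets. The change concerns only how events are counted and takes no view on how they should be managed.

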### *Adverse event* reporting and harms

A complete list of serious adverse events (SAEs) is presented in Table 2. As expected, mortality is relatively high in this patient population; therefore, death will not be reported as SAE. SAEs are chosen based on possible relation with blood transfusions.

Each type of SAE and the total number of SAE is reported in the eCRF and do not have to be reported separately. The annual report of SAEs is communicated to the Ethics Committee of the trial coordinator center, as a responsibility of the study coordinator and the primary investigator. As the interim analysis did not report potential harm differences between groups, the SAE report to the Data Safety Monitoring Committee (DSMC) was decided only on the basis of the annual evaluation of the Ethics Committee.

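### The anaphylactic-reaction row of Table 2 counts skin signs alone or hemolysis alone and omits acute reactions with neither, so its label and definition need reconciling

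*Protocol article*

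**What the plan says.** Table 2 of the protocol article has a row labelled "Anaphylactic reaction to RBC transfusion". Its whole definition is "Muco-cutaneous signs (i.e., urticaria, pruritus) and/or hemolytic anemia within 24 h after transfusion".

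The section Adverse event reporting and harms gives the table its status and use:

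- Completeness: "A complete list of serious adverse events (SAEs) is presented in Table 2".
- Selection: "SAEs are chosen based on possible relation with blood transfusions".
- Counting: "Each type of SAE and the total number of SAE is reported in the eCRF".

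The section Interim analysis says that the look at 300 patients was to "assess for protocol compliance, main outcome, and SAEs". Separately, Interventions: modifications counts an "error in type/cross-match between donor and recipient" as a protocol violation. No other part of the article redefines the row or gives hemolytic reactions a row of their own.

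**The concern.** The rule does not measure the event it names. Its and/or makes each element sufficient alone, and the skin signs are spelled out as two specific findings. The row contains no respiratory or circulatory element. It can therefore take in events that are not anaphylactic and leave out acute reactions that show neither skin signs nor hemolysis.

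At stake is how readable one harm is. Only three rows are tied by definition to a transfusion: this one, TRALI and TACO. Anyone reading the by-type table, whether the safety committee, the ethics committee or a later reader, would take the entries in this row for anaphylaxis. The SAE total inherits the same entries.

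**Working it through.** **Step 1. Literal reading.** The article states no rate or count for this event, so there is no figure to reproduce. The check is to apply the row to four hypothetical records.

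| Record | This row | Elsewhere in Table 2 |
|---|---|---|
| Itching only, within 24 h of a unit | Counted | No other row needed |
| Hemolysis only, within 24 h | Counted, under the anaphylaxis label | No separate row |
| Acute respiratory or circulatory reaction without skin signs or hemolysis | Not counted | Only if another row's own criteria are met |
| Hemolysis first seen after 24 h | Not counted | No row names it |

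For the third record, the severe hypotension row requires "MAP < 65 mmHg for at least > 1 h, not responding to fluid therapy and needing vasopressor therapy, in the absence of active bleeding". A short episode would not meet that. The TRALI and TACO rows require lung infiltrates.

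**Step 2. Which comparisons move.** Let *u* be units per patient, *q* the per-unit chance of a qualifying event that is not anaphylactic, *t* the per-unit chance of a true anaphylactic reaction, and *s* the share of true reactions that show a qualifying sign. Then, per arm:

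- recorded patients = 397 × [1 − (1 − (q + s·t))^u]
- true patients = 397 × [1 − (1 − t)^u]

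The 397 per arm comes from the section Sample size. The values of *u*, *q*, *t* and *s* are all assumptions, varied below (liberal / restrictive).

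| Units | q | t | s | Recorded | True | Difference, recorded vs true | Ratio, recorded vs true |
|---|---|---|---|---|---|---|---|
| 2 / 1 | 0.1% | 0.005% | 0.8 | 0.83 / 0.41 | 0.040 / 0.020 | 0.4 vs 0.02 | 2.00 vs 2.00 |
| 2 / 1 | 2% | 0.005% | 0.8 | 15.75 / 7.96 | 0.040 / 0.020 | 7.8 vs 0.02 | 1.98 vs 2.00 |
| 3 / 1 | 2% | 0.005% | 0.8 | 23.39 / 7.96 | 0.060 / 0.020 | 15.4 vs 0.04 | 2.94 vs 3.00 |
| 2 / 0.5 | 0.1% | 0.005% | 0.8 | 0.83 / 0.21 | 0.040 / 0.010 | 0.6 vs 0.03 | 4.00 vs 4.00 |
| 2 / 1 | 1% | 0.05% | 0.5 | 8.10 / 4.07 | 0.397 / 0.198 | 4.0 vs 0.20 | 1.99 vs 2.00 |

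The recorded difference runs from 0.4 to 15.4 patients, or 0.4/397 = 0.1 to 15.4/397 = 3.9 percentage points. The ratio barely changes, because true and mislabelled events both rise with units given.

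**Step 3. Net direction.** Per unit, the row adds about *q* and misses (1 − s)·t. It overcounts on balance only if q > (1 − s)·t. The largest missed rate used above is 0.5 × 0.05% = 0.025% and the smallest *q* is 0.1%, so every line shows an overcount. That follows from the chosen inputs and not from the article.

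**Step 4. Share of entries that are the named event.** This is s·t / (q + s·t). With s = 0.5, t = 0.005%, q = 2% it is 0.0025/2.0025 = 0.1%. With s = 0.8, t = 0.05%, q = 0.1% it is 0.04/0.14 = 29%. No useful bound results.

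**The case against.** The best defence is that the row captures genuine transfusion harms under a poor name. Allergic and hemolytic reactions are effects of the strategies being compared, so an excess in the arm transfused below 9 g/dL is a real difference. That stands, and it confines the fault to the label and the seriousness attached to it.

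Other points that stand:

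- Lack of a severity threshold does not set this row apart. Venous thrombotic events need only a diagnosis, and infections follow an external definition. Those rows do describe what their labels say; this one does not.
- SAE counts are not among the outcomes in the section Study outcomes. Infection rate, organ dysfunction and the composite with death also bear on harm.
- Cross-match errors are recorded as violations in the eCRF. That captures the error, however, and not a resulting hemolytic reaction.
- The eCRF is not shown and may hold skin and hemolytic components separately. If so, the correction is easier, but the printed row still merges them.

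A reader might infer that the definition biases the arm comparison against the liberal strategy. The documents do not support this: with a constant reaction rate per unit, the ratio is nearly unchanged. Unblinded recording of a subjective sign such as itching could change it, but the article gives no evidence that this happened. A reader might also infer that almost none of the entries would be true anaphylaxis. Step 4 shows that this depends wholly on rates the article does not give.

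**Conclusion.** The mismatch is real and follows from the wording alone. As written, skin signs alone or hemolysis alone count as a serious anaphylactic event, and an acute reaction with neither is left out of the row. The by-type count is mislabelled, and the total carries the same entries.

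The effect on absolute counts and the risk difference is larger in the arm transfused more. That rests on the triggers in Interventions: description, and on the small randomized study cited under Explanation for the choice of comparators, which found less transfusion with the restrictive strategy. The size cannot be derived from the documents, and net inflation is an assumption. The tabulated values are illustrations only.

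The primary outcome, sample size and type I error are untouched. This is a minor correction to safety reporting.

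**What to change.** - Rename the row for what it captures: allergic or hemolytic reaction to transfusion.
- Before database lock, re-read its entries from the eCRF and source notes and report skin-only, anaphylactic and hemolytic reactions on separate lines. The sponsor should set and document the clinical criteria before the re-reading starts.
- Mask allocation and Hb values during the re-reading where possible. Masking may be incomplete, because Hb can reveal the arm.
- Keep the row in the SAE total and show that total with and without the skin-only entries. Dropping the whole row would remove hemolytic reactions from the total.

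The cost is a wording change and a re-reading of the entries in one row. The work is largely retrospective: the section Trial status gives 791 recruited against a target of 794, with data collection ending in June 2023. Reactions that were never entered because they did not fit the row may not be recoverable, and the report should say so.
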